## Abstract

**Background:**

Men are at higher risk then women of developing cardiovascular disease (CVD), and male taxi drivers are a particularly high-risk group because of their typically unhealthy behaviours, such as poor eating habits, smoking and sedentary lifestyle. However, only two studies of behavioural interventions targeting taxi drivers have been identified, one of which reported a high attrition rate. Therefore, an eHealth intervention co-designed by taxi drivers may prove more acceptable and effective. The aim of this study is to assess the feasibility an eHealth intervention (ManGuard) to reduce CVD risk in male taxi drivers.

**Methods:**

A randomised wait-list controlled trial will be conducted with a sample of 30 male taxi drivers to establish feasibility, including recruitment, engagement, and retention rates. Program usability and participant satisfaction will be assessed by a survey completed by all participants at 3 months after allocation. Additionally, an in-depth qualitative process evaluation to explore acceptability of the intervention will be conducted with a subset of participants by semi-structured telephone interviews. Preliminary efficacy of ManGuard for improving key CVD-related outcomes will be assessed, including biomarkers (total cholesterol, HDL cholesterol, LDL cholesterol, triglycerides, and total/HDL cholesterol ratio), blood pressure, anthropometry (body mass index, body fat percentage, and waist circumference), physical activity (accelerometery, and self-report) and psychosocial status (health-related quality of life, self-efficacy, and social support). Outcomes will be assessed at baseline, 7 weeks, and 3 months after group allocation. The wait-list control group will be offered access to the intervention at the completion of data collection.

**Discussion:**

eHealth interventions show potential for promoting behaviour change and reducing CVD risk in men, yet there remains a paucity of robust evidence pertaining to male taxi drivers, classified as a high-risk group. This study uses a randomised controlled trial to assess the feasibility of ManGuard for reducing CVD risk in male taxi drivers. It is envisaged that this study will inform a fully powered trial that will determine the effectiveness of eHealth interventions for this high risk and underserved population.

**Trial registration:**

This trial has been registered prospectively on the ISRCTN registry on 5 January 2022, registration number ISRCTN29693943

**Supplementary Information:**

The online version contains supplementary material available at 10.1186/s40814-022-01163-4.

## Background

Cardiovascular disease (CVD), cancer, chronic pulmonary disease, and diabetes account for approximately 80% of non-communicable disease (NCD) related deaths and develop as the result of a combination of genetic, physiological, environmental, and behavioural factors [74]. However, behavioural risk factors such as tobacco use, excessive alcohol consumption, poor dietary choices, and physical inactivity, are most associated with the development of NCDs [31].

CVD remains the leading cause of NCD-related mortality worldwide, accounting for one-third of all deaths in 2019 [75]. Males are at a higher risk of developing CVD than females throughout their lifetime until older age [73]. In the United Kingdom (UK), including Northern Ireland, where 12% of the population are living with CVD and 30% of CVD-related deaths will be premature [8], men have a higher incidence of myocardial infarction and of diabetes.

### Taxi driving and CVD risk

Taxi driving is a male dominated occupation [53] and is associated with an increased risk of CVD [13]. Factors include long working hours and traffic congestion, causing prolonged psychological stress [13, 70], as well as sleep deficiency, irregular work patterns, noise, and regular exposure to air pollution [76]. There is a higher prevalence of modifiable CVD-related risk factors and behaviours among taxi drivers, including having high blood pressure, being overweight or obese, lacking fruit and vegetables, smoking, consuming excessive alcohol and spending long periods sedentary [4, 13, 17, 22, 70, 76].

The long periods of sedentary behaviour and subsequent lack of physical activity directly affect the development of CVD [66], associated with elevated blood pressure, weight gain and poor cholesterol profiles in taxi drivers [3, 12]. Physical activity can mitigate such adverse effects in this population [67], for example, by protecting against hypertension and counter-balancing the negative impact of age, working hours, and weight [69].

Despite the increased risk of CVD and high prevalence of CVD-related risk factors in taxi drivers [3–5, 13, 22, 23, 27, 48, 51, 54, 69], only two studies of behaviour change interventions targeted at this group have been identified [14, 23]. Both interventions were aimed at increasing physical activity through walking, assessing steps [14, 23], days walked, and amount of time walked [14]. Improvements in physcial activity were observed for participants receiving either intervention, with signficant improvements observed for all walking-related measures in one [14]. However, a major limitation to the study by Gany et al. [23] was the high rate of participant attrition (61%). To improve engagement and reduce attrition of men in health behaviour change interventions, a gender-sensitised approach to development is recommended [7, 55].

### eHealth interventions for behaviour change

eHealth offers a means of tailoring interventions to meet the needs of end-users and has the potential to improve intervention uptake, adherence, and success [65]. Defined as “the use of technology to improve health, well-being and healthcare” [65], eHealth provides participants with an easily accessible and easy to use intervention [45]. The ease of access and use may be of benefit to taxi drivers, presenting as a hard-to-reach group due to the remote nature of the occupation. A recent systematic review and meta-analysis reported the success of eHealth interventions in promoting behaviour change among those living with NCDs [18]. Another recent systematic review and meta-analysis by us found similar findings for the reduction in CVD risk in men, with improvements in body weight, body mass index (BMI), waist circumference and blood pressure observed as a result of eHealth interventions [39].

However, weaknesses of eHealth interventions include poor adherence and high rates of attrition [33, 35]. To counter this, it is important that consideration is given to the needs of the end-users, iteratively developed, grounded in behaviour change theory and rigorously evaluated prior to the dissemination of findings [46, 50, 65].

The IDEAS (Integrate, Design, Assess, and Share) framework has been proposed for the design, development, and evaluation of eHealth interventions [46], and was utilised for the development of ManGuard. This 10-phase framework draws on the strengths of several approaches for eHealth interventions including design thinking, user-centred design, behaviour change theories, evaluation, and dissemination [46]. The framework recommends an intervention be pilot tested to assess preliminary efficacy, providing an opportunity to refine the study protocol prior to progressing to a definitive randomised controlled trial [46].

Due to greater levels of engagement in CVD-related risk behaviours, behaviour change interventions could prove beneficial for this high-risk group. However, little appears to have been done to help reduce the observed risk, with significant participant attrition observed in one of the two trials studying this population. In particular, the provision of an eHealth intervention may prove beneficial due to the ease of access and use for a hard-to-reach population. Guided by the IDEAS framework, a novel eHealth intervention (ManGuard) has been developed alongside end-users through an iterative process, ensuring program acceptability and user satisfaction. This paper describes the study protocol for a feasibility randomised controlled trial to pilot test ManGuard, an eHealth intervention that aims to reduce CVD risk in male taxi drivers in Northern Ireland.

### Research aims and objectives

This study aims to assess the feasibility of ManGuard. Study objectives are the following:
Primary—to assess:◦ Acceptability: recruitment, retention, and engagement rates◦ Program usability and participant satisfaction: process evaluation and surveySecondary—to assess the preliminary efficacy of ManGuard compared to usual care in improving the following outcomes:◦ Clinical indices: CVD biomarkers (cholesterol, glucose), blood pressure, anthropometry (BMI, waist circumference, body fat percentage)◦ Physical activity◦ Psychosocial status: health related quality of life, self-efficacy, social support

## Methods

### Study design

The study will be a randomised wait-list controlled trial followed by a process evaluation. A wait-list control is employed to increase acceptability of the research protocol to the participants in the control group, and thereby to decrease attrition effects [16]. Both groups will be matched on participant demographics, with those in the wait-list control group receiving the intervention following the final data collection at 3 months after allocation. Semi-structured telephone interviews will be conducted at 3 months as part of a process evaluation.

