### Participants

#### Eligibility criteria for participants

Adult males (≥ 18 years)Working part-time or full-time as a taxi driver in Northern IrelandHaving access to the internet and a smartphone that allows for the downloading of mobile applications.

As this is a feasibility randomised controlled trial, no formal power calculation will be completed to determine sample size. Recommendations on the appropriate sample size for pilot and feasibility studies vary greatly, with sample sizes ranging between 24 and 50 participants [57]. We have chosen a sample size of 30 for this study, as recommended by the National Institute for Health Research (NIHR) in the UK [30].

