### Randomisation

Participants will be randomly allocated by blocked randomisation to the intervention and wait-list control group using the Statistical Package for the Social Sciences (SPSS V.24). Due to the small sample size, blocked randomisation is deemed an appropriate technique for reducing the risk of bias and ensuring equal allocation between groups [20]. The wait-list control group will not be provided with any materials relating to the intervention or recommendations on how they can improve on their current lifestyle habits to maintain a ‘true control’. Upon the completion of data collection at 3 months, participants in the wait-list control group will be offered access to the intervention. The randomisation procedure will be carried out by a researcher not affiliated with the study. Participant allocation will be placed in a sealed envelope and opened by the lead researcher upon completion of baseline data collection.

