### Data collection, management, and analysis

#### Demographic characteristics

A survey will be disseminated during the participants’ first visit to the NICRF to gather demographic data. Information will pertain to the participants’ age, postcode, education level, employment status, years worked as a taxi driver, working hours, lifestyle factors, knowledge of CVD, and presence of chronic diseases diagnosed by a health professional. The information gathered form the survey will be explored to gain an understanding of factors that may influence a participant’s decision to take part in the study.

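### The protocol says the groups will be matched on demographics, but the blocked randomisation it describes does not ensure that

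*Protocol article*

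**What the plan says.** The Study design section introduces the trial with "The study will be a randomised wait-list controlled trial followed by a process evaluation" and then says, without qualification, that "Both groups will be matched on participant demographics". It does not say which demographics or by what procedure.

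The Randomisation section gives the procedure: "Participants will be randomly allocated by blocked randomisation to the intervention and wait-list control group", generated in SPSS by a researcher outside the study. Its reason for the method is that "blocked randomisation is deemed an appropriate technique for reducing the risk of bias and ensuring equal allocation between groups". On concealment it says: "Participant allocation will be placed in a sealed envelope and opened by the lead researcher upon completion of baseline data collection". It names no demographic factor.

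The Demographic characteristics section says when the data are obtained: "A survey will be disseminated during the participants’ first visit to the NICRF to gather demographic data". The use it gives them is different from matching; they will be "explored to gain an understanding of factors that may influence a participant’s decision to take part in the study".

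The Quantitative analysis section plans repeated measures ANOVA between groups over three time points and mentions no matching factor or demographic covariate. On size, the protocol says: "We have chosen a sample size of 30 for this study".

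**The concern.** Matching is a design property. It has to be produced by the allocation procedure, and the procedure described does not produce it. A reader who takes the Study design sentence at face value will believe that the arms are alike on demographics by construction, and will give the between-arm efficacy differences more credit than 30 randomised men can support. Whoever generates the sequence also faces two statements that have not been reconciled: one asks for demographic matching, and the other describes blocks with no factor to match on.

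Preliminary efficacy against usual care is a stated secondary objective, and the Discussion expects the study to provide the basis for a definitive trial. The comparability of the arms should therefore be described correctly.

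**Working it through.** The protocol gives no figure for balance, so there is nothing to reproduce. The check has two parts: a comparison of the sections, and an illustration of how much chance imbalance blocking leaves.

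**Comparison of the sections**

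| Section | Role of demographics |
|---|---|
| Study design | Groups said to be matched on them |
| Randomisation | None stated; blocking justified by less bias and equal allocation |
| Demographic characteristics | Collected at the first visit to understand the decision to take part |
| Quantitative analysis | Described at baseline; no role stated in the between-group comparison |

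Only the first row claims matching, and no other row supplies a means of achieving it.

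**Illustration of chance imbalance**

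Inputs: 30 men in total (Eligibility criteria) and equal allocation (Randomisation), so 30/2 = 15 per arm. The 0.5 SD threshold, the number of characteristics, their correlation and the block sizes are assumptions; the protocol gives none of them.

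1. One continuous characteristic. The standardised difference between arm means has standard error sqrt(2/15) = 0.365. For a 0.5 SD gap, z = 0.5/0.365 = 1.37, and the two-sided probability is 0.171. For gaps of more than 0.25 SD and 0.75 SD the probabilities are 0.494 and 0.040.

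2. Effect of blocking. In 40,000 simulated trials for each of block sizes 2, 4 and 6, the probability of a gap above 0.5 SD was 0.170, 0.172 and 0.169. Group sizes never differed by more than 2. Blocking therefore does its own job and leaves covariate imbalance where it was.

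3. Several characteristics. If independent, the probability that at least one of k exceeds 0.5 SD is 1 − (1 − 0.171)^k: 0.608 for k = 5 and 0.777 for k = 8.

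4. Correlated characteristics. Several of the listed items are likely to be related, such as age and years as a driver. For five equally correlated characteristics, simulation gives about 57% at correlation 0.3, 51% at 0.5 and 42% at 0.7.

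5. A yes/no characteristic. If 10 of the 30 men have a trait, the hypergeometric probability of a gap of 4 or more men between arms (4/15 = 27 percentage points) is 0.245.

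**The case against.** The best reply is that this is one loose phrase in a condensed article. Matched may mean no more than comparable as groups, which randomisation provides in expectation. Block size and strata are details that an article commonly leaves to the full protocol, and stratified blocks would be compatible with the text because demographics are collected before the envelope is opened. The three time points are baseline, 7 weeks and 3 months, so the baseline outcome is already in the repeated measures model, and a constant difference between arms drops out of the group-by-time contrast. The probabilities would apply to any unstratified trial of 30, and the protocol itself says the study is not powered and will be interpreted cautiously.

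Much of this stands, and it rules out several stronger readings that a reader might infer:

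- That balance is absent. Randomisation balances demographics on average and may do so in this sample; balance is only not ensured.
- That covariates are left out because the authors rely on matching. The protocol gives no such reason, and an analysis plan not shown may add covariates.
- That the trial needs a matched-pairs analysis. No pairs are described anywhere.

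What does not stand is the defence that detail has merely been left out. Matching is asserted as something that will happen, and the only allocation method described, with its own stated rationale, does not deliver it. If strata exist, the Randomisation section is incomplete on the very point that the Study design section advertises; if they do not, the Study design sentence is wrong. The repeated measures model does not settle the matter either. When the arms differ by chance on the outcome at baseline, the group-by-time contrast remains sensitive to that gap through regression to the mean, which adjustment for the baseline value handles. A demographic difference can also affect how men change over time.

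**Conclusion.** The point holds as a contradiction between the Study design and Randomisation sections: demographic matching is claimed, and the method described ensures equal numbers only. The finding rests on the text and does not depend on the probabilities.

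Those probabilities show that the difference is not academic at this size: about 17% for one continuous characteristic beyond 0.5 SD with 15 per arm, and about 61% for at least one of five under independence, falling to 42% at the highest correlation tried. The 0.5 SD threshold and the count of five are illustrative choices.

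The consequence is moderate. Recruitment, retention, engagement, usability and satisfaction are the primary outcomes, and progression depends on recruitment, retention and acceptability. None of these compares the arms, so the progression decision is unaffected. What is affected is how the secondary preliminary-efficacy comparisons will be read.

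**What to change.** 1. In Study design, replace the matching clause with a statement along these lines: blocked randomisation will balance group sizes; the groups are not matched on demographics; baseline characteristics will be shown by arm.

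2. In Quantitative analysis, state that the between-arm comparisons at 7 weeks and 3 months will be adjusted for the baseline value of the outcome. That value is already collected for every secondary outcome.

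Together these cost a few lines of text, with no new data and no change to allocation.

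3. Only if demographic balance is truly intended: name one or two factors and the stratification method in the Randomisation section, generate the sequence accordingly, and include the factors in the analysis. This is a larger change. Each man's factor values must be known at allocation, and the sealed envelopes would have to be prepared by stratum. With 30 men, more than one or two factors would leave very small strata. Minimisation would go further and replace the pre-prepared envelopes altogether.

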### Research setting

The research will be conducted in a community setting with male taxi drivers working in Northern Ireland.

### Participants

#### Eligibility criteria for participants

Adult males (≥ 18 years)Working part-time or full-time as a taxi driver in Northern IrelandHaving access to the internet and a smartphone that allows for the downloading of mobile applications.

As this is a feasibility randomised controlled trial, no formal power calculation will be completed to determine sample size. Recommendations on the appropriate sample size for pilot and feasibility studies vary greatly, with sample sizes ranging between 24 and 50 participants [57]. We have chosen a sample size of 30 for this study, as recommended by the National Institute for Health Research (NIHR) in the UK [30].

### Recruitment

As a result of taxi drivers working both independently and for large companies, recruitment will be conducted via the online social media platform ‘Facebook’ to increase reach. This method of recruitment was employed previously for the recruitment of participants to aid in the co-design of the ManGuard intervention. A Microsoft Forms link, with a brief description of the study, will be posted into two separate Facebook groups dedicated to taxi drivers working across Northern Ireland, estimated as having 4200 members. The link will be posted weekly, with recruitment open for a duration of 17 months, ceasing once the target sample has been achieved. Those who are interested will provide their name and email address, with the lead researcher then sending a participant information sheet with the inclusion/exclusion criteria.

Those that meet the inclusion criteria will be invited to the Northern Ireland Clinical Research Facility (NICRF) to be formally recruited to the study and complete baseline testing. During the participants’ final visit to the NICRF, participants in the intervention group will be offered the opportunity to participate in the semi-structured telephone interviews as part of a process evaluation. Verbal consent will be obtained and recorded at the commencement of the telephone interview, with participants made aware of their right to withdraw from the interview at any time.

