#### Qualitative analysis

Semi-structured telephone interviews for collecting data on participant satisfaction, experience, and program usability will be audio recorded and transcribed verbatim. Transcripts will be analysed using conventional content analysis using an inductive approach for the coding and categorising of data. Content analysis involves a systematic approach for exploring large amounts of textual information [63], suitable for intervention refinement [49]. All participants in the intervention group will be invited to complete the telephone interviews, with interviews ceasing once data saturation is achieved [37]. Members of the research team will be involved in the qualitative analysis of data and will assess data saturation throughout the telephone interview process.

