### Progression criteria

Progression to a definitive trial will be determined by the following progression criteria for participant recruitment, utilised previously in pilot and feasibility studies [11, 38].75-100% of the target sample size (30) recruited to the study will warrant progression to a definitive trial50-74% of the sample size (30) recruited to the study will warrant progression to a definitive trial following necessary adjustments to barriers of recruitment outlined during the process evaluation25-49% sample size (30) recruited to the study will only warrant progression to a definitive trial if changes to the protocol are made by both the research team and the potential future co-applicantsLess than 25% of the sample size (30) recruited to the study will indicate that the trial is unlikely to progress.

Progression criteria for retention rates will follow the criteria below [29]: > 80% retention rate will warrant progression to a definitive trial60-80% retention rate will warrant progression to definitive trial following necessary adjustments to counter attrition < 60% retention rate will indicate progression to a definitive trial is unlikely

Participant satisfaction will be assessed through the process evaluation and will provide information on whether the intervention was feasible, including the process of randomisation. Progression to a definitive trial will be dependent on acceptability, with necessary modifications indicated by the participants being made prior to progressing.

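### The interview offer is tied to the final clinic visit and to the intervention arm, so men who miss that visit may never be asked and no control is interviewed about randomisation or waiting

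*Protocol article*

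**What the plan says.** **Who is interviewed, and when.** Study design sets the timing: "Semi-structured telephone interviews will be conducted at 3 months as part of a process evaluation". The Recruitment section gives the only operational step for the invitation, at the "final visit to the NICRF, participants in the intervention group will be offered the opportunity to participate in the semi-structured telephone interviews". The Qualitative analysis section words the invitation without any condition of attendance: "All participants in the intervention group will be invited to complete the telephone interviews, with interviews ceasing once data saturation is achieved". Both sections confine the interviews to the intervention arm.

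**What the interviews cover.** The Qualitative analysis section states their purpose: "Semi-structured telephone interviews for collecting data on participant satisfaction, experience, and program usability will be audio recorded and transcribed verbatim".

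**What the results are used for.** Under Progression criteria, participant satisfaction is assessed through the process evaluation, which "will provide information on whether the intervention was feasible, including the process of randomisation". The same paragraph makes progression depend on acceptability, with changes that participants ask for made first. The 50-74% recruitment band allows progression "following necessary adjustments to barriers of recruitment outlined during the process evaluation". For retention of 60-80%, the text is that this "retention rate will warrant progression to definitive trial following necessary adjustments to counter attrition". It does not say where the information for those adjustments comes from.

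**Other sources.** The Abstract and Feasibility measures have all participants, controls included, complete a survey at 3 months. The Abstract describes it as assessing usability and satisfaction. Feasibility measures also lists weekly usage analytics, and the Quantitative analysis section reports recruitment and retention in a CONSORT flow diagram.

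**The concern.** Two groups matter to the progression decision and are poorly reached.

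The first is intervention-arm men who stop attending. The Recruitment and Qualitative analysis sections differ on whether these men are invited, and the only described way of making the offer is face to face at a visit they do not attend. Their reasons for leaving bear directly on acceptability and on the changes a definitive trial would need. The protocol itself treats attrition as a central risk: the Background cites 61% in one of only two earlier behavioural studies in taxi drivers, and the Discussion returns to attrition as a common limitation of trials in men.

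The second is the wait-list controls. They are asked to wait 3 months without materials or lifestyle advice. Study design justifies the wait-list on the ground that it makes the protocol more acceptable to controls and so reduces attrition. Controls are best placed to say whether that worked, yet none is interviewed.

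At stake is the balance of the acceptability evidence. If it comes mainly from men who liked the programme enough to stay, it will tend to look better than it should, and the modifications carried forward may miss what drove others out.

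**Working it through.** The plan gives no figure for the number of interviews, so there is nothing to reproduce. The check is a comparison of the texts, followed by a count.

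**1. Does the text reach men who miss the final visit?**
- Recruitment: the offer is made in person at the last clinic visit. A non-attender gets no offer.
- Qualitative analysis: "All participants in the intervention group will be invited to complete the telephone interviews". On its face this includes non-attenders, but it describes no route for inviting them.
- 3-month survey: completed at the assessment time point, so it is likely to miss the same men.

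The two sections are inconsistent. The one that says how the offer is made leaves non-attenders out.

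**2. Does the text reach controls on randomisation?**
- Interviews: intervention arm only, in both sections.
- Survey: reaches controls, but is described as covering usability and satisfaction. Controls have no access to the app until data collection ends, and nothing says that the survey asks about randomisation or waiting.

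**3. Is there another source of reasons for dropout?**
- Analytics (logins, modules accessed, time per module, tracker use): show when use fades.
- CONSORT flow diagram: described as presenting recruitment and retention rates.
- Baseline survey: allows leavers and stayers to be compared on work and lifestyle.

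None of these is described as recording why a man left.

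**4. How many men are affected?**

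Inputs: target sample 30 (Participants); equal allocation (Randomisation), so 30 / 2 = 15 per arm; retention band 60-80% (Progression criteria). Assumptions: full recruitment, equal retention in both arms, and the Recruitment rule followed literally.

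Intervention men offered an interview = 15 × retention. Intervention men not offered one = 15 × (1 − retention).

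| Retention | Offered | Intervention men not offered |
|---|---|---|
| 100% | 15 × 1.00 = 15 | 0 |
| 80% | 15 × 0.80 = 12 | 3 |
| 60% | 15 × 0.60 = 9 | 6 |
| 39% (illustration: the earlier study's 61% attrition) | 15 × 0.39 = 5.85, about 6 | about 9 |

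Throughout the middle retention band, where adjustments against attrition are required, 3 to 6 of the 15 men given the app would not be asked about it in interview. Stopping at saturation can only reduce the number actually interviewed.

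**The case against.** **The Recruitment section gives a time for the offer; it does not say that nobody else may be asked.** This is fair. The Qualitative analysis wording is unconditional, the interviews are by telephone, and email addresses are collected at first contact, so nothing in the design prevents an invitation to a man who has stopped attending. The full protocol may say how withdrawn men are contacted. What remains is a conflict between two sections of the same text, which needs reconciling either way.

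**The protocol does not require the interviews to explain attrition.** This stands. A reader might infer such a requirement, but the retention criteria name no information source, the listed interview topics are satisfaction, experience and usability, and the only numeric band tied to the process evaluation concerns recruitment. The link to attrition is reasonable because no other source of reasons is described, but it remains an inference.

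**There is evidence on attrition.** This also stands. It would be wrong to conclude that the 60-80% band has nothing to act on: analytics, baseline data and the participant flow all bear on who leaves and when. The gap is narrower, namely that no source of stated reasons is described.

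**Controls are heard through the survey and cannot comment on an app they have not used.** This is partly right. Adding the 15 controls to the 3 to 6 non-attenders gives 18 to 21 of 30, and a reader might take that as the number of men left unheard. It counts only those outside the interviews: controls who attend at 3 months complete the survey, and they have no experience of the app to report. Intervention men were also randomised and can comment on that. They cannot describe being allocated to wait.

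**Numeric progression results do not depend on who is interviewed.** This is correct, and it limits the seriousness of the point.

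**Conclusion.** The concern holds in a limited form. The Recruitment and Qualitative analysis sections disagree on whether intervention men who miss the final visit are invited to interview. Followed literally, the Recruitment section leaves them out. No control is interviewed, although the process evaluation is expected to speak to randomisation, and the survey that does reach controls is not described as covering it.

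The consequence is a likely, not certain, tilt of the acceptability evidence towards men who stayed. The size is 3 to 6 of 15 intervention men at 80% to 60% retention, on the assumptions of full recruitment, 15 per arm and equal retention. The documents do not show that dropouts are certain to be absent, that the interviews must explain attrition, or that evidence on attrition is lacking altogether.

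This should be fixed, because acceptability conditions the progression decision and the correction is cheap. It does not undermine the trial or its recruitment and retention thresholds.

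**What to change.** 1. Align the Recruitment section with the Qualitative analysis section: invite every man allocated to ManGuard by telephone or email at 3 months, or at withdrawal if earlier, whether or not he attends the clinic.
2. State that interviewing will not stop on saturation until the available non-completers have been approached.
3. Obtain controls' views on randomisation and waiting, either by a few short telephone interviews or by items added to the existing 3-month survey. Added survey items cost less, but would probably still miss controls who do not attend.

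The cost is revised protocol and consent wording and a few extra calls by the existing interviewer. Some men who have left will decline, so the number approached and the number interviewed should be reported by completion status.
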